## Abstract

Spinal cord injury and traumatic brain injury are major causes of long-term disability and are often complicated by spasticity, a motor disorder characterized by increased muscle tone and exaggerated reflexes that significantly impair quality of life. Current diagnostic methods lack the sensitivity needed to accurately predict the severity of injury or the onset and progression of spasticity. Trauma-induced calcium dysregulation activates calpains, a family of proteases that cleave sodium channels, disrupting their inactivation and increasing persistent sodium currents. This cascade drives the overexcitability of motoneurons, contributing to the development of spasticity. Consequently, sodium channel fragments have emerged as promising biomarkers that link injury mechanisms to clinical outcomes. The present SpasT-SCI-T clinical trial protocol aims to evaluate sodium channel fragments as blood biomarkers for assessing the severity of spinal cord and traumatic brain injuries, as well as their potential to predict clinical outcomes, including the development of spasticity. This prospective, multicenter, case-control and cohort study involves 40 participants: 20 individuals with spinal cord injury, 10 individuals with traumatic brain injury, and 10 healthy controls. Blood samples are collected within six hours of injury and at follow-up points over six months. Clinical outcomes, including spasticity (assessed using the Modified Ashworth Scale), neurological recovery (measured by the American Spinal Injury Association Impairment Scale and Glasgow Coma Scale), and quality of life (evaluated using the Short Form-36 Health Survey), are analyzed in correlation with biomarker levels. We anticipate that calpain-mediated sodium channel fragments will transform the management of central nervous system injuries by enabling early diagnosis, improving prognostic accuracy, and guiding personalized therapeutic strategies. The clinical trial is registered on ClinicalTrials.gov (NCT06532760, January 10, 2024), with Assistance Publique–Hôpitaux de Marseille as the sponsor.

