## Introduction

Spinal cord injury (SCI) is a tragic condition with lifelong physical, psychological, and economic consequences, affecting millions of individuals worldwide [1–3]. Accurate and timely assessment of its severity is paramount for predicting outcomes and guiding therapeutic interventions. However, current diagnostic methods, which rely primarily on clinical examinations and imaging, lack the sensitivity required for precise evaluation, especially during the critical acute phase [4–6]. This diagnostic gap underscores the urgent need for novel, reliable biomarkers to improve clinical decision-making.

One of the most prevalent and disabling complications of SCI is spasticity, which affects up to 75% of patients within the first year post-injury [7,8]. Spasticity, classically defined as hypertonia with a velocity-dependent increase in stretch reflexes [9], encompasses a spectrum of clinical manifestations, including clonus, exaggerated reflexes, muscle spasms, and involuntary leg crossing [10,11]. These symptoms severely disrupt daily activities, quality of life, and rehabilitation efforts. Without early and effective management, spasticity progresses to complications such as muscle shortening, joint contractures, and painful pressure sores [12,13]. The unpredictable onset and variable severity of spasticity, ranging from mild stiffness to severe, uncontrollable spasms, pose significant challenges for clinicians, emphasizing the urgent need for reliable predictive biomarkers [14,15].

Advances in our understanding of spasticity pathophysiology have highlighted promising targets for biomarker discovery [16,17]. Secondary injury processes in SCI trigger molecular cascades, including excessive glutamate release, intracellular calcium overload, and calpain activation [18,19]. Calpains, calcium-activated proteases, cleave Nav1.6 voltage-gated sodium channels [20–22], which are predominantly expressed in spinal motoneurons [23–25]. This proteolysis disrupts the normal inactivation of Nav1.6 channels, leading to an upregulation of persistent sodium currents (I_NaP_) [20–22]. The pathological I_NaP_ drives motoneuron hyperexcitability and sustained depolarizations (plateau potentials), directly contributing to spasticity in both animals [26–31] and humans [32–34].

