### Study design

The SpasT-SCI-T study is a prospective, multicenter observational trial performed in France. The study employs a combination of case-control and cohort designs to address its primary and secondary objectives. The inclusion of patients will officially begin on March 17, 2025 and end on September 20, 2026. A total of 40 participants are recruited, divided into three groups:

1**Group 1 (Healthy Controls):** Ten healthy volunteers provide baseline blood samples for comparison.2**Group 2 (SCI Patients):** Twenty patients with acute traumatic SCI confirmed by imaging and no associated TBI.3**Group 3 (TBI Patients):** Ten patients with acute TBI confirmed by imaging and no associated SCI.

The trial consists of three phases:

1**Inclusion Phase:** Participants are enrolled into one of the three study groups based on predefined eligibility criteria.2**Acute Phase (0–14 days):** This phase focuses on the immediate response to trauma, capturing rapid changes in sodium channel fragment levels during the critical early period. Blood samples are collected within 6 hours post-trauma and at multiple time points (Days 1, 3, 5, 7, and 14) to monitor early biomarker kinetics.3**Late Follow-Up Phase (3 and 6 months):** The late follow-up phase assesses long-term changes in sodium channel fragment levels and their association with recovery trajectories and clinical outcomes, including the onset and severity of spasticity. Blood samples are collected during follow-up consultations at 3 and 6 months post-trauma. A 6-month follow-up was selected as clinical signs of spasticity typically stabilize between 2 and 6 months post-injury, with electrophysiological measures showing minimal change thereafter [38].

The CONSORT diagram in Fig 1 provides details on the timeline for enrollment, interventions, and assessments across the participant groups, while the overall study design is summarized in Fig 2.

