1**Temporal Dynamics of Sodium Channel Fragments:** The temporal kinetics of sodium channel fragments are analyzed to characterize their dynamic expression and persistence during the acute and chronic phases of injury. Longitudinal changes in fragment levels are assessed from the baseline (acute phase) through follow-up visits at 3 months (M3) and 6 months (M6). These data are related with key clinical and functional outcomes to evaluate the role of sodium channel fragments as potential prognostic biomarkers. For SCI patients, changes in neurological function are monitored using the American Spinal Injury Association (ASIA) Impairment Scale, which provides detailed assessments of sensory and motor function recovery. For TBI patients, functional recovery is evaluated using the Glasgow Outcome Scale (GOS) and the more granular Glasgow Outcome Scale-Extended (GOSE), which capture subtle variations in recovery trajectories. For both groups, quality of life is assessed using the Short Form Health Survey (SF-36), a comprehensive tool that evaluates health-related quality of life across physical, mental, and social dimensions. These correlations aim to establish the predictive value of sodium channel fragment levels for neurological recovery, functional outcomes, and overall quality of life, providing a deeper understanding of the molecular mechanisms underlying injury progression and recovery.2**Spasticity and Biomarker Levels in SCI Patients:** The relationship between sodium channel fragment levels and spasticity is specifically investigated in SCI patients. Spasticity is assessed during follow-up visits at M3 and M6 using the Modified Ashworth Scale (MAS), a widely used tool for grading muscle tone. The relationship between MAS scores and fragment levels is evaluated using correlation analyses. This correlation is expected to provide evidence of the prognostic utility of sodium channel fragments in predicting the onset and severity of spasticity. These analyses aim to establish the prognostic utility of sodium channel fragments in predicting the onset, progression, and severity of spasticity, providing a molecular link between injury mechanisms and clinical outcomes. Such insights may inform personalized therapeutic strategies for managing spasticity in SCI patients.3**Injury Severity and Biomarker Associations:** The study investigates the association between sodium channel fragment levels and injury severity in both SCI and TBI patients. For SCI patients, neurological severity is assessed using the ASIA Impairment Scale, which evaluates the level and completeness of spinal cord injury through sensory and motor function tests. For TBI patients, the severity of brain injury is determined using the GCS, which provides a standardized assessment of consciousness based on eye, verbal, and motor responses. By correlating sodium channel fragment levels with these established severity metrics, the study aims to elucidate the relationship between molecular biomarkers and clinical injury severity, enhancing the understanding of the pathophysiology of CNS trauma and informing future diagnostic approaches.

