### Justification of sample size

The study includes a total of 40 participants distributed as follows: 20 patients with spinal cord injury (SCI), 10 patients with traumatic brain injury (TBI), and 10 healthy controls. The selection of 20 SCI patients is based on the annual admission rates for SCI at the study institution, ensuring a representative sample of the population served. The inclusion of 10 TBI patients is justified to account for potential confounding factors arising from the overlapping but distinct injury mechanisms of SCI and TBI. Furthermore, 10 healthy controls are included to provide a robust baseline for sodium channel fragment levels, facilitating a balanced comparison across the three groups.

This sample size is sufficient to detect meaningful trends and associations between sodium channel fragments and clinical outcomes, including spasticity, while maintaining feasibility within the scope of a pilot study. The findings will generate preliminary evidence regarding the diagnostic and prognostic utility of sodium channel fragments in neurological injuries and will guide the design of larger-scale clinical trials.

Given the exploratory nature of this study, no formal interim analyses are planned. As the trial involves minimal-risk procedures, such as blood sampling, no pre-specified stopping rules have been established. In the event of significant deviations from the protocol or unforeseen safety concerns, the trial steering committee will consult the Ethics Committee to determine whether adjustments or study termination are necessary. All such decisions will be transparently documented and communicated to relevant stakeholders, including regulatory authorities, to ensure compliance with ethical standards.

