### Statistical methods

The primary objective of this study is to quantify sodium channel fragments in blood samples and compare their levels across the three participant groups: healthy controls (Group 1), SCI patients (Group 2) and TBI patients (Group 3). To address this objective, statistical analyses will begin with group comparisons.

1**Group Comparisons:** For normally distributed data, one-way analysis of variance (ANOVA) will be employed to identify differences in sodium channel fragment levels among the three groups. If data are not normally distributed, the Kruskal-Wallis test will be applied as a non-parametric alternative. Post-hoc analyses will follow these tests to assess pairwise comparisons, using Tukey’s test for ANOVA or the Mann-Whitney U test for non-parametric data.2**Effect Size Calculation:** Effect sizes (e.g. Cohen’s d for t-tests or η² for ANOVA) will be calculated to quantify the magnitude of differences between groups.

For secondary outcomes, analyses will focus on the temporal kinetics of sodium channel fragments and their correlation with clinical outcomes.

1**Temporal Kinetics:** Changes in fragment levels over time, measured at baseline (6 hours), during the acute phase (Days 1, 3, 5, 7), and at follow-up (Months 3 and 6), will be analyzed using repeated-measures ANOVA for normally distributed data. For non-normally distributed data, the Friedman test will be used. Bonferroni corrections will be applied during multiple comparisons.2**Spasticity Correlation:** The relationship between sodium channel fragment levels and spasticity severity in SCI patients will be assessed using Spearman’s rank correlation coefficients, with spasticity evaluated at Months 3 and 6 using the Modified Ashworth Scale (MAS).3**Subgroup Analysis (SCI Severity):** Subgroup analyses will investigate whether sodium channel fragment levels differ by injury severity. In SCI patients, severity will be categorized based on the American Spinal Injury Association (ASIA) Impairment Scale grades (A–D). Similarly, spasticity onset will be analyzed as a binary outcome (presence vs. absence). For TBI patients, the Glasgow Coma Scale (GCS) will be used to classify injury severity, enabling comparisons of sodium channel fragment levels across defined severity subgroups.

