Additional statistical methods will include multivariable linear regression models to adjust for potential confounders, including age, sex, injury severity (ASIA grades A–D for SCI, GCS scores for TBI), and concurrent medications (antispasmodics, analgesics, antiepileptics) as primary factors, as well as additional variables from Table 3 such as comorbidities (diabetes, organ failure), trauma context (type of accident), and biological parameters (hemoglobin, renal clearance) where statistically significant or clinically relevant, informed by prior literature [14,21]. This ensures that observed associations between sodium channel fragment levels and outcomes such as spasticity are robust and not influenced by baseline characteristics. Receiver operating characteristic (ROC) curves will be generated to identify threshold levels of sodium channel fragments that differentiate SCI from TBI or predict spasticity onset. To address missing data, multiple imputation methods will be applied, minimizing bias and preserving the validity of the analyses.

Continuous variables will be expressed as means with standard deviations for normally distributed data or medians with interquartile ranges for non-normally distributed data. Categorical variables will be summarized as frequencies and percentages. For all primary and secondary analyses, a two-tailed p-value < 0.05 will be considered statistically significant. Patients who die before the 3-month follow-up will be excluded from spasticity-related analyses due to insufficient time for spasticity development, but all data collected up to the time of death will be included in secondary analyses, such as demographic characterization and early biomarker levels.

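### Prognostic utility for spasticity is tied to an unadjusted correlation and a fragment-only ROC curve; an ASIA-adjusted regression is planned, but nothing measures prediction beyond the baseline ASIA grade

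*Protocol article*

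**What the plan says.** The rationale is comparative. The Introduction says that clinical examination and imaging "lack the sensitivity required for precise evaluation, especially during the critical acute phase", and the Abstract anticipates that fragments will help by "enabling early diagnosis, improving prognostic accuracy, and guiding personalized therapeutic strategies".

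The Outcomes section (secondary outcome 2) then names the evidence. Of the correlation between fragment level and MAS score it says: "This correlation is expected to provide evidence of the prognostic utility of sodium channel fragments in predicting the onset and severity of spasticity". Statistical methods specifies Spearman's rank correlation with MAS at Months 3 and 6, and plans ROC curves for "threshold levels of sodium channel fragments that differentiate SCI from TBI or predict spasticity onset". Both use the fragment alone.

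Among the additional methods, the same section plans a multivariable linear regression. Age, sex, injury severity (ASIA grade in SCI patients) and concurrent medications are its primary factors. Its stated purpose is to show that associations with outcomes such as spasticity are not due to baseline characteristics.

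Secondary outcome 3 examines whether fragment levels follow ASIA grade, and the Discussion presents fragments as a marker of injury severity.

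**The concern.** A marker improves prognosis only relative to what is already known. Baseline ASIA grade is known for every SCI patient at inclusion. If fragments follow severity, as the authors expect, and severity is related to later spasticity, then fragments will correlate with spasticity even if they carry no further information. An unadjusted Spearman coefficient and a fragment-only AUC cannot tell that case from a marker that adds something.

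The adjusted regression does address independent association, but it does not close the gap:

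- The prognostic statement is attached to the correlation, not to the regression.
- The regression yields a coefficient, not a measure of discrimination, and as a linear model it does not serve the binary onset outcome or the ROC curve.
- It has many terms for at most 20 patients, so a null adjusted result would say little. The unadjusted correlation could then become the headline by default.

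The sample size section says the pilot will guide larger trials. A fragment with no added value could be carried forward on the strength of an association that ASIA grade already explains.

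**Working it through.** **Inputs from the article.** The spasticity analysis uses the SCI group only: "Twenty patients with acute traumatic SCI confirmed by imaging and no associated TBI". Its size rests on feasibility: "The selection of 20 SCI patients is based on the annual admission rates for SCI at the study institution". The test level: "a two-tailed p-value < 0.05 will be considered statistically significant". Spasticity frequency: up to 75% (Introduction), so with 20 patients about 0.75 × 20 = 15 spastic and 5 non-spastic. There is no stated power, effect size or expected correlation for this analysis, so there is no figure to reproduce.

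**Assumptions.** The marker–severity and severity–spasticity correlations, and the distribution of ASIA grades, are not given and are assumed.

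**Step 1: a marker that only mirrors severity.** Simulated trials of 20 patients, with 4,000 per scenario. ASIA is four ordered grades cut from a latent severity, MAS is ordinal, and 75% are spastic. The marker is related to spasticity only through severity, with a marker–severity correlation of 0.5 to 0.7. The partial Spearman is

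r(F,M·A) = [r(FM) − r(FA)·r(MA)] / √{[1 − r(FA)²][1 − r(MA)²]},

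where F is fragment, M is MAS and A is ASIA grade, tested on 20 − 3 = 17 df.

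| Severity–spasticity correlation (assumed) | Unadjusted Spearman significant | Partial Spearman given ASIA significant |
|---|---|---|
| 0.3 | about 9–13% | about 5–7% |
| 0.7 | 28–53% | 5–7% |

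At 0.7 the fragment's mean AUC is 0.66–0.74, against 0.82 for ASIA grade alone.

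The results move with the set-up. One run at 0.3 gave only 6–9%. A variant that ties the marker directly to the observed grade, with marker–ASIA correlations of 0.5–0.9 and ASIA–spasticity correlations of 0.5–0.7, gave 16–87% unadjusted and mean AUC 0.62–0.82. In that variant the fragment was significant in 4–5% of runs in a linear model with ASIA terms.

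**Step 2: how much the planned regression can show.** Slopes for the primary factors plus the fragment: age 1, sex 1, ASIA 3, medications 3, fragment 1, total 9. Residual df = 20 − 1 − 9 = 10, before any optional comorbidity, trauma or laboratory variable and before deaths ahead of Month 3 are removed. The partial correlation detectable with 80% power, adjusting for k terms, is tanh[(1.960 + 0.842)/√(20 − 3 − k)]:

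- k = 0 (unadjusted): tanh(2.802/√17) = 0.59
- k = 1 (ASIA as one ordered score): tanh(2.802/√16) = 0.60
- k = 3 (ASIA as three indicators): tanh(2.802/√14) = 0.63
- k = 8 (all primary factors): tanh(2.802/√9) = 0.73

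Conditioning on ASIA grade alone costs little. The full adjustment costs a good deal.

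**Step 3: is the fragment AUC minus the ASIA AUC a usable test of added value?** Take a fragment that truly adds information: severity–spasticity 0.7, marker–severity 0.5, independent effect 0.3. The mean AUC difference was about −0.02, and its bootstrap interval lay above zero in only about 5% of trials. The partial Spearman was significant in 45%. That difference compares two rival predictors. It does not show what the fragment adds to ASIA.

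**The case against.** The strongest reply is that the safeguard is already there. The regression places ASIA grade in its first tier of covariates and is aimed at this very confounding. In the simulations such adjustment holds the error for a pure severity mirror at about 5%. A reader might infer that the plan ignores ASIA grade, or that a severity mirror would inevitably be declared prognostic. The article supports neither reading. The adjusted result will exist, and the authors may give it due weight.

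It can also be said that the study is an exploratory pilot, that improved prognostic accuracy is an anticipated benefit rather than an objective, and that the objective under Study aims is only to evaluate the relation between fragment levels and spasticity, which the planned analyses do. Choosing a reference predictor for a ROC curve is detail that an analysis plan not shown here may hold. With about five non-spastic patients, added value cannot be settled in this study.

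All of that limits the point. What remains is that the article itself says which result is evidence of prognostic utility, and that result is the unadjusted correlation. The inference does not follow from it, whatever a later analysis plan adds.

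**Conclusion.** The point holds in limited form. ASIA adjustment is planned, but the prognostic statement rests on an unadjusted correlation, the spasticity ROC curve has no ASIA reference, and no analysis measures prediction beyond ASIA grade. A marker that only mirrors severity could be reported as prognostic.

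The size is uncertain. It is small if severity and spasticity are weakly related (about 9–13% significant at a correlation of 0.3, and 6–9% in one run) and substantial if they are strongly related (28–53% at 0.7), against 5–7% given ASIA. These figures rest on assumed correlations of 0.5–0.7 between marker and severity, 75% spasticity and all 20 patients evaluable. The mechanism does not depend on the exact values. The matter is one of interpretation and reporting in a pilot, and does not invalidate the design.

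**What to change.** 1. Report the fragment–MAS Spearman correlation also as a partial correlation given baseline ASIA grade alone, with its 95% CI. Base any statement of prognostic utility in secondary outcome 2 on that estimate, labelled exploratory. Keep the fuller regression as a supporting analysis.
2. Beside the fragment's ROC curve for spasticity onset, report the AUC of ASIA grade alone and, descriptively, of ASIA plus fragment from a penalised or optimism-corrected model, each with a bootstrap interval.
3. Do not use the fragment AUC minus the ASIA AUC as the test of added value.

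Cost: two or three extra estimates from data already collected, and a change of wording. The downside is imprecision. For a partial correlation near zero with 20 patients and ASIA as one score, the approximate 95% limits are ±tanh(1.96/√16) = ±0.45, and the AUC intervals will be wide with so few non-spastic patients. The text should say so, so that a null result is not read as proof of no added value.
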